**Procedure for MRI (Visit 4)**

For all participants who consent to MRI and have no contraindication. Participants will receive structural MRI scanning to determine site of lesion, Resting State Functional Connectivity fMRI, and Diffusion Tensor Imaging.

**Procedures for Treatment (Visit 5-19)**

The following procedures will be performed:

1. Measure the electrode location on the scalp (Right cerebellum: 1 cm below the inion and 4 cm lateral)

2. Soak the 2 sponge electrodes in saline solution and place inside rubber electrode holders.

3. Place the cathode electrode under the designated area on the right cerebellum

located during the electrode positioning process (marked with a star) and reference electrode anode on the right deltoid muscle.

4. Connect the electrode cables to the Soterix tDCS device.

5. Start the tDCS device and enter the code. Soterix clinical trial tDCS device includes a software for true operator blinding where the PI can have preset codes for tDCS and sham trials including the dosage and the clinician will enter the codes and the device will present either tDCS or sham depending on the code that was assigned.

6. The Speech Language Pathologist will start the Semantic Feature Analysis Treatment (SFA). Participants will receive SFA treatment for 60 minutes and tDCS for the first 25 minutes. SFA treatment employed in study will include 50 items and their relevant features from eight semantic categories. Items included in each participant's treatment list will be determined based on performance on a picture-naming task. The naming task will consist of 200 items across eight semantic categories (food (including fruits and vegetables), animals, transportation, clothing, music, sports, furniture, toys). The naming task will be administered once. To qualify for treatment, an item must be named incorrectly. To avoid effects of repeated exposure, items included on the naming task will be constrained such that they do not occur in the primary outcome variable (PNT). Therapy tasks will be administered through a computer with clinician assistance using Microsoft Powerpoint. Participants will be trained on 7-12 items per session depending on each participant’s aphasia severity. The treatment protocol will be adapted from Doyle, Dickey and colleagues (Gravier et al., 2018; Evans et al., 2021). The treatment will proceed according to a series of steps including naming aloud the target picture, generating semantic features, naming aloud the target picture again, and generating a sentence using the target word. Participants will be asked to generate semantic features for each target picture in five categories: group [superordinate category], function [use/action], description [physical properties], context [location], and other/personal [association]. A three-level cueing hierarchy will be used to elicit features, consisting of general prompt (e.g., “How would you describe this?”), followed by a relevant directed question (e.g., “What does this feel like?”) and a binary forced-choice question (e.g., “Is this item smooth or rough?”). Only verbal responses will be accepted during treatment.

7. Record any Adverse Events (AE) experienced during the treatment session or since the last visit on the AE log.

8. Assess and record the participant's comfort rating using the Wong-Baker FACES Pain Rating (Wong & Baker, 1988) Scale following treatment completion.

Procedures for Neurological Examination (Will be administered on visit 1, 2, or visit 3)

All participants will be monitored closely for safety and neurological functioning during the duration of the study. In addition to the comfort ratings recorded daily, a neurological examination will be administered during Visit 1, 2, or 3. If there is any change noted in the neurological status by the clinician during the duration of the study, then [name] will be notified, and the neurological examination will be repeated.

*b. Study duration and number of study visits required of research participants.*

Participants will undergo screening, language assessments, and MRI (visits 1-3). Eligible participants will receive treatment for 3-5 weeks (3-5 sessions in a week: total 15 sessions). Study duration will be approximately 7-8 months and the number of visits for each participant will be 23.

*c. Blinding, including justification for blinding or not blinding the trial, if applicable.*

Randomization and Blinding

All participants, the members of the study team who administered the assessments and treatments as well as the study biostatistician performing the statistical analyses will be blinded. Participants will be randomized 1:1 (cathodal tDCS or sham tDCS), stratified by site (JHH vs Howard County), aphasia type (fluent vs. non-fluent, classified using WAB-R), and severity (classified using WAB-R Aphasia Quotient in 4 categories (very severe aphasia: 0–25, severe aphasia: 26–50, moderate aphasia: 51–75, and mild aphasia: 76-93.8). Covariate-adaptive randomization method developed by Pocock and Simon, 1975 will be implemented in REDCap. This method ensures balance on important baseline covariates for each treatment arms by calculating the difference in these covariates (site, aphasia type and severity) each time a participant needs be randomized and then randomizes with high probability (80%) to the arm that corrects the imbalance on covariates. The SLP will enter the baseline and eligibility information of a participant prior to enrollment on REDCap. If the participant’s eligibility is confirmed, then the algorithm implemented in REDCap will evaluate the treatment arm distribution in participants already randomized and then generate treatment allocation group (sham or tDCS) based on the randomization scheme. Each participant will receive a unique six-digit codes (provided by manufacturer of the tDCS stimulator), which will instruct the stimulator to deliver either active stimulation or placebo (sham). These codes will be entered into REDCap prior to starting the study. The study coordinator will enter the codes in REDCap.

*d. Justification of why participants will not receive routine care or will have current therapy stopped*

Participation in this study will not disrupt any current care or therapy.

*e. Justification for inclusion of a placebo or non-treatment group*

Both groups will receive semantic feature analysis treatment, a commonly used treatment for naming deficits in aphasia. It is currently unknown whether or not cerebellar tDCS augments the effect of semantic feature analysis in the chronic phase after stroke. Therefore, a sham group is justified.

*f. Definition of treatment failure or participant removal criteria*

Participants will be removed from the study if they are unable to comply with task instructions or tolerate the tDCS procedure.

*g. Description of what happens to participants receiving therapy when study ends or if a participant’s participation in the study ends prematurely*

When the study ends, participants will continue to receive management with [name] or their own neurologist as usual (generally follow-up visits every about 6). If a patient’s participation in the study ends prematurely s/he will still receive care as before. In sum, termination of the study or termination of participation in it will not affect regular therapy he or she may be receiving.

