In order to minimize the need for research-only in-person visits, telemedicine visits will be substituted for portions of clinical trial visits where determined to be appropriate and where determined by the investigator not to increase the participants risks. For the current study, we will utilize telemedicine visits when appropriate for consenting and for all the assessments visits (visits 1- 3, 20-23). Prior to initiating telemedicine for study visits the study team will explain to the participant, what a telemedicine visit entails and confirm that the study participant is in agreement and able to proceed with this method. Telemedicine acknowledgement will be obtained in accordance with the Guidance for Use of Telemedicine in Research. In the event telemedicine is not deemed feasible, the study visit will proceed as an in-person visit. Telemedicine visits will be conducted using HIPAA compliant method approved by the Health System and within licensing restrictions.

Visit 1: During the first visit, participants will sign informed consent and undergo screening assessments. This will include tDCS and MRI safety screening, and aphasia diagnosis

Visit 2 and 3: This involves detailed language testing (see below) including computerized naming assessments. This will be the baseline language testing.

Visit 4: Participants may be asked to get structural MRI (to determine site of lesion) and fMRI (resting state). If the participant does not have a lesion in the right cerebellum, the participant will be able to start intervention. This visit is only for participants who consent to MRI and have no contraindication.

Participants will also undergo neurological exam in visit 1, 2 or 3.

Visit 5-19: This will involve the treatment sessions. Prior to the start of treatment, participants will be randomly assigned to receive sham plus SFA or active tDCS plus SFA.

Visit 20: This visit will involve 1-week post-treatment language testing. Assessment of primary and secondary outcome variables.

Visit 21: This visit will involve 1-month post-treatment language testing. Assessment of primary and secondary outcome variables.

Visit 22: This visit will involve 3-months post-treatment language testing. Assessment of primary and secondary outcome variables.

Visit 23: This visit will involve 6-months post-treatment language testing. Assessment of primary and secondary outcome variables.

Procedures for Visit 1

The following procedures will be performed:

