Adverse events will be monitored during the entire visit by the study team. The families will be given telephone numbers of study team as well. The study physician ([name]) and the DSMB will be notified immediately if any adverse events are reported. The DSMB will determine if the adverse event is a serious adverse event. Adverse events will be monitored until they are resolved or clearly determined to be due to a subject’s stable or chronic condition or intercurrent illness. In the case of any unexpected adverse events involving risks to participants or others that are related/possibly related to the research, a Protocol Event Report will be prepared by the Study Coordinator, the PI will be informed immediately, and the IRB will be contacted within 10 days as per Johns Hopkins Medicine IRB policy; deaths will be reported within 72 hours. Also, as required by IRB policy, any unexpected adverse device effects, potential breaches of confidentiality, unresolved participant complaints will be promptly reported to the IRB. Any other adverse events that do not require prompt reporting will be summarized and reported to the IRB at the time of continuing review.

Plan for dealing with incidental findings: All MRI scans will be reviewed by Co-I and board-certified neurologist ([name]), and any suspicious abnormalities will be referred to a board-certified neuroradiologist. If unexpected abnormalities - incidental findings - are seen (which is unlikely, as every patient will have had a clinical MRI as part of their evaluation for stroke), the patient will be asked permission to contact the primary care physician about the abnormality, and will be offered a timely appointment with a neurologist ([name]) if appropriate.

1. *Legal risks such as the risks that would be associated with breach of confidentiality.*

Participation in this study should not put participants in any legal risk, even in the case of a breach of confidentiality. We will undertake every effort to keep the information in the study confidential. Participants will be assigned a code number for the scans in order to keep the information confidential. Consent forms and source documents will be maintained at the PI lab in locked cabinet. All digital data will be stored on a password-protected and encrypted format in a manner that is Johns Hopkins IRB compliant.

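### The only scheduled adverse-event look-back and log step is written for treatment Visits 5-19, so events after the last session have no scheduled question at Visits 20-23

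*Protocol*

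**What the plan says.** The adverse-event (AE) log appears in one place in the Protocol. Section 4, under the heading "Procedures for Treatment (Visit 5-19"), item 7, reads: "Record any Adverse Events (AE) experienced during the treatment session or since the last visit on the AE log".

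The overview in Section 4 describes the first post-treatment visit as follows: "Visit 20: This visit will involve 1-week post-treatment language testing. Assessment of primary and secondary outcome variables". The visits at 1, 3 and 6 months are described in the same terms, ending with "Visit 23: This visit will involve 6-months post-treatment language testing. Assessment of primary and secondary outcome variables". These visits can be remote: "we will utilize telemedicine visits when appropriate for consenting and for all the assessments visits (visits 1- 3, 20-23").

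Two other places bear on safety after treatment:

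- The neurological examination part of Section 4 states: "All participants will be monitored closely for safety and neurological functioning during the duration of the study". The steps it names are the daily comfort ratings, one neurological examination at Visit 1, 2 or 3, and a repeat examination if the clinician notes a change.
- Section 8, in the plan for reporting problems, states: "Adverse events will be monitored during the entire visit by the study team". It adds that families receive telephone numbers for the study team, that reported AEs go at once to the study physician and the DSMB, and that AEs are followed until resolved or attributed to another condition.

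**The concern.** Item 7 looks back from each session over the interval since the previous visit. The protocol therefore already treats events between visits as worth asking about. That question is last scheduled at session 15. From then on, no written step asks what has happened since the participant was last seen, although the participant is seen four more times.

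What is at stake is how complete the AE record is once the full 15-session course has been given. The abstract says the trial is to provide the basis for a Phase III trial, so AE information on the completed course is of use. The participants have aphasia, and a reporting route that depends on them or their families telephoning unprompted is a weak substitute for a direct question. A seizure at home illustrates the problem: observation during a visit would miss it, while a look-back question would probably find it. Events not asked about at the time are hard to recover later, and no analysis can restore them.

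**Working it through.** **Visit count.** From the visit list in Section 4: Visits 1-3 (3) + Visit 4 (1) + Visits 5-19 (15) + Visits 20-23 (4) = 23. This reproduces the 23 visits per participant stated in Section 4b. A written AE-log step exists for 15 of the 23 visits. All four post-treatment visits lack one.

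**Which intervals the look-back covers.** The last scheduled look-back, at Visit 19, covers the gap from Visit 18 to Visit 19. The following intervals have no scheduled look-back:

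- session 15 to Visit 20: about 1 week
- Visit 20 to Visit 21: 1 week to 1 month after treatment
- Visit 21 to Visit 22: 1 to 3 months after treatment
- Visit 22 to Visit 23: 3 to 6 months after treatment

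**Whether another provision fills the gap.** Each safety provision outside item 7 is taken in turn:

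| Provision | Applies after Visit 19? | Asks about events since the last visit? |
|---|---|---|
| Daily comfort rating (Section 4) | No, it is recorded at treatment sessions | No |
| Neurological examination (Section 4) | Only as a repeat, if a change is noted | No |
| AE monitoring during visits (Section 8) | Yes, it is not limited to treatment visits | No, it covers the visit itself |
| Telephone numbers for families (Section 8) | Yes | No, it depends on an unprompted call |
| Follow-up of AEs to resolution (Section 8) | Yes | No, it applies to events already known |

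Some capture therefore continues after Visit 19, but none of it is a scheduled look-back.

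**Size of the first unasked interval.** Inputs: 60 participants enrolled and 10% attrition (Section 7, sample size); 1 week from session 15 to Visit 20 (Section 4).

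- No attrition: 60 × 1 week = 60 person-weeks
- Planned attrition applied: 60 × (1 − 0.10) = 54; 54 × 1 week = 54 person-weeks

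For scale, treatment lasts 3 to 5 weeks (Section 4b). With all 60 participants, the period covered by item 7 is 60 × 3 = 180 to 60 × 5 = 300 person-weeks.

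These figures measure time without a scheduled question. The protocol gives no AE rate for the post-treatment period, so they cannot be turned into a number of missed events.

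**The case against.** The best defence is that the protocol does commit to safety monitoring for the whole study. It provides for AE monitoring at visits without limiting this to treatment visits, and it gives families a way to report. The overview gives each of Visits 20-23 only two short generic sentences and does not even name the primary naming test there. It describes Visits 5-19 just as briefly, also without mentioning AEs. Silence in such an overview does not prove that staff will not ask. Section 8 also describes mostly minor effects and reports no serious adverse effect across more than 33,200 tDCS sessions, so nothing in the document points to late or cumulative harm.

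Much of this stands, and it rules out several stronger readings that a reader might infer:

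- *That post-treatment events are never asked about, or that safety monitoring ends at Visit 19.* Sections 4 and 8 keep general monitoring and a reporting route open. Capture is unstructured; it is not excluded.
- *That item 7 contradicts the promise of study-long monitoring.* A specific step at treatment sessions is compatible with a general commitment. The commitment lacks a matching procedure after treatment.
- *That an active-versus-sham AE comparison is compromised.* The protocol's objectives, outcomes and statistical plan contain no such comparison.
- *That only about 10% to 16% of safety time is covered.* Taking 6 months as 26 weeks, the arithmetic is 3/(3 + 26) = 10.3% to 5/(5 + 26) = 16.1%. The denominator is mostly follow-up without stimulation, so the ratio does not measure lost safety information.
- *That the primary endpoint is affected because the gap falls just before Visit 20.* That endpoint is change in naming and does not depend on the AE log.

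The objection does not supply a scheduled look-back. Visits 5-19 have a detailed procedure list that includes the AE step, and no such list exists for Visits 20-23. The general statements do not say that anyone asks about the time between visits.

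**Conclusion.** The point holds as a gap in procedure. The scheduled AE look-back and log step is written only for Visits 5-19. After session 15, events are captured through observation at later visits or spontaneous report, while Section 4 promises monitoring for the duration of the study. The week after the completed course, about 54 to 60 person-weeks, and the follow-up to 6 months have no scheduled AE question. Logged events may therefore be understated, by an amount the document does not allow one to estimate.

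This rests on two assumptions: that staff follow the procedures as written, and that Visit 20 falls about one week after session 15. The person-week range depends only on how the planned attrition is applied. The primary naming analysis, sample size and error rates are unaffected. This is a cheap improvement to safety capture and does not call the trial's main conclusion into question.

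**What to change.** Extend item 7 (AEs since the last visit, recorded on the AE log) to Visit 20. Extend it to Visits 21-23 as well, at least for serious and neurological events. State that it applies equally when these visits are held by telemedicine. The visit procedures would then match the study-long monitoring promised in Section 4. Any time window for comparing AEs between arms can be left to the SAP.

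The cost is one question and one log entry at visits that already take place. The downside is that a few more unrelated background events will be recorded over the 6 months. No treatment, dose or visit schedule changes.

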**7. Study Statistics**

1. *Primary outcome variable*

The primary outcome will be defined as the change in accuracy of naming measured by the Philadelphia Naming Test, one week after the end of semantic feature analysis (SFA)

1. *Secondary outcome variables*

In addition to the primary outcome, several secondary analyses will be conducted. (1) Trained Picture Naming. We will assess if tDCS has an effect on naming items trained during treatment (trained picture naming). We will assess change in trained picture naming before treatment to within 1 week after the end of treatment. Follow up testing will be done at one month, three months, and six months after the completion of the treatment. (2) Discourse. We will assess change in discourse abilities, as measured by the change in the total Content Units (CU) and syllable per CU produced by the participants during connected speech. Participants will be required to describe the Cookie Theft Picture from the Boston Diagnostic Aphasia Examination. (3) Functional Communication Skills. We will also measure changes in everyday functional communication skills assessed with the Communication Activities of Daily Living, third edition (CADL-3). (4) Finally, we will administer 3 tests from the Research Outcome Measurement in Aphasia-Core Outcome Set (ROMA-COS) at baseline, 1-week post treatment, and at 1-month, 3-month, and 6-month follow-up time points. The WAB-R will be administered as a part of the baseline testing. We will also assess changes in emotional well-being (measured by General Health Questionnaire (GHQ)-12 and quality of life (measured by Stroke and Aphasia Quality of Life Scale (SAQOL-39).

1. *Statistical plan including sample size justification and interim data analysis*

Statistical Analysis

Aim 1: Determine whether cathodal tDCS to the right cerebellum combined with evidenced-based anomia treatment improves picture naming.

Hypothesis1a: 15 sessions of cathodal tDCS over the right cerebellum + SFA treatment will be associated with greater improvement in naming untrained pictures (as measured by the change in PNT),1-week post treatment, compared to sham + SFA.

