Statistical analysis**:** The analyses will follow the Intention-to-treat (iTT) principle *where participants are analyzed based on the group to which they are randomized regardless of early termination, missing data or errors in randomization detected post hoc.* The primary outcome variable will be change in accuracy of naming untrained items as measured by the PNT within 1 week after semantic feature analysis ends.

The primary hypothesis is H_0_: mu_1_ = mu_2_ versus H_A_: mu_1_ $\neq$ mu_2_, where mu_1_ is the mean change in accuracy of naming untrained items between baseline and 1-week post- semantic feature analysis in the tDCS group and mu_2_ is the mean change in accuracy of naming untrained items between baseline and 1 week post semantic feature analysis in the sham group. Average Treatment Effect (ATE) will be estimated using linear regression model with change in accuracy of naming untrained items at 1 week as the dependent variable and group assignment (real tDCS versus sham) as the independent variable. ATE is estimated by the coefficient for the group assignment.

As a secondary analysis, we will consider non-parametric mixed models for analyses of functional response over time. In particular, let Y_ijk_ = u_ik_ + fk(j) + e_ij_ where Y_ij_ is the the outcome for subject i on occasion j (0, 1, 3, 6) within treatment arm k. (Thus, both i and k are necessary to identify a subject). No covariates are necessary because of the randomization (though see Aim 2). f_k_(j) is a functional model we will estimate using quadratic regression splines with knot points at each of the time points. Given there are so few time points, we will not penalize the spline fit. A non-parametric estimate of a treatment effect is given by f_2_ – f_1,_ which can show time-specific treatment effects when evaluated at specific points j. This will also demonstrate the rate (when and if) at which TCDS effects ebb. An overall effect can be estimated by simply taking the integral of f_2_ – f_1_ (i.e. the functional averaged effect over time). A null hypothesis of zero represents no time averaged effect of the treatment. Given that we will use regression splines, every estimator reduces to standard contrasts of regression parameters, and thus can be implemented in any statistical software package.

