
1. T-test comparing the treatment effect across median splits of the moderating variables performed separately, one at a time.
2. A non-parametric modeling approach using spline based linear models testing whether the potential moderating variables interact with the treatment effect over time. We will consider two variations of this approach:
   1. One that assumes linearity
   2. One that assumes non-parametric functions

Sample Size Determination

We used the data from the PI’s K99 study (crossover trial) to estimate the variability of untrained naming score. 52 participants (26 per group) will give us 80% statistical power to detect 0.7 SD difference in change in accuracy of naming untrained items at 1-week post treatment between the study arms. This was done using Wald test for group assignment coefficient in linear regression at 0.1 level of statistical significance. The effect size (0.7SD) is a bit conservative compared to the difference observed on group comparison for 21 participants (10 in tDCS and 11 in sham) in the K99 data, when the tDCS was administered in Phase 1. We propose to enroll 60 participants to account for 10% attrition.

Missing Data

*The analyses will follow the Intention-to-treat (iTT) principle where participants are analyzed based on the group to which they are randomized regardless of early termination, missing data or errors in randomization detected post hoc. To minimize possible biases, analyses will be by intention to treat; any missing data will be addressed with the technique of multiple imputation (Ball et al., 2002; Rubin, 2009), generally recognized as best for handling missing data (Little et al., 2012).*

1. *Early stopping rules. N/A*

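### Section 4f ends study participation, not only study treatment, for participants who cannot comply or tolerate tDCS, leaving their primary outcome to imputation

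*Protocol*

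**What the plan says.** Protocol section 4f, on treatment failure and removal, consists of one rule: "Participants will be removed from the study if they are unable to comply with task instructions or tolerate the tDCS procedure". The visit list in section 4a places allocation before the first session: "Prior to the start of treatment, participants will be randomly assigned to receive sham plus SFA or active tDCS plus SFA". Section 4g covers early exit and speaks only of usual care. It says that if a patient's "participation in the study ends prematurely s/he will still receive care as before". No section says that the post-treatment assessments (Visits 20 to 23) continue after removal.

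Section 7 makes the primary outcome the change in PNT accuracy one week after therapy ends. It promises analysis by randomised group "regardless of early termination, missing data or errors in randomization detected post hoc", and under Missing Data it adds that "any missing data will be addressed with the technique of multiple imputation". The sample size paragraph plans 26 evaluable participants per arm and 60 enrolled, to allow for 10% attrition.

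**The concern.** An intention-to-treat analysis is strongest when outcomes are sought from everyone randomised, whether or not they finished treatment. Section 4f works against that. A participant who stops because of tDCS, or who cannot manage the tasks, leaves the study, and the natural reading is that the 1-week PNT is then not taken. The analysis keeps the person in the assigned arm, but with an imputed value where an observed one was often within reach.

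Both grounds for removal are plausibly related to outcome. Difficulty with task instructions may go with severity, and the trial stratifies down to an Aphasia Quotient of 0-25. Someone who cannot tolerate stimulation has not had the full 15 sessions. If such losses also differ between arms, in number or in outcome, the estimated treatment difference can be biased. Nor can a statistical analysis plan recover data that were never collected, so the protocol is the place to settle this.

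**Working it through.** **Timing.** Allocation precedes the first session (section 4a), and tDCS is given only in the treatment sessions. Removal for not tolerating tDCS is therefore always after randomisation. Removal for not following task instructions may be.

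**The plan's own figure.** Inputs from section 7: difference 0.7 SD, power 80%, a two-sided hypothesis, and testing "at 0.1 level of statistical significance".
- n per arm = 2(1.645 + 0.842)² / 0.7² = 25.2, rounded up to 26. This matches the protocol. Power at 26 per arm is 81.0% (normal) or 80.1% (noncentral t).
- 52 / 0.9 = 57.8, so 58 are needed; 60 covers it and leaves 54 (27 per arm) after 10% loss. Power is then 81.4%, or 84.9% if all 60 are assessed, with the effect held at 0.7 SD.

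The sample size is sound, and the removal rule does not change it. The possible cost is bias.

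**Bias if the missing outcomes are not recovered.** In one arm, let a fraction r be removed, and let their mean change lie g SD below the mean m of those who stay. The arm's true mean is (1 − r)m + r(m − g) = m − rg. An analysis that in effect gives removed participants the mean of those who stay returns m, which is too high by rg. The bias in the treatment difference is therefore

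r(tDCS) × g(tDCS) − r(sham) × g(sham), or g × [r(tDCS) − r(sham)] when g is the same in both arms.

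The documents give neither r nor g, so all values below are assumptions. Each row totals 6 removed of 60 (30 per arm), which assigns the whole 10% attrition allowance to this rule. The last column is the rejection probability of the two-sided t-test at nominal 0.10 when the true difference is zero.

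| Removed, tDCS vs sham | g (SD) | Bias (SD) | Share of 0.7 SD | Type I error |
|---|---|---|---|---|
| 10% vs 10% | any, equal | 0 | 0% | 0.100 |
| 15% vs 5% | 0.25 | 0.025 | 4% | 0.101 |
| 15% vs 5% | 0.5 | 0.05 | 7% | 0.106 |
| 15% vs 5% | 1.0 | 0.10 | 14% | 0.122 |
| 20% vs 0% | 0.25 | 0.05 | 7% | 0.106 |
| 20% vs 0% | 1.0 | 0.20 | 29% | 0.187 |

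With more removed from sham, the sign reverses. The 20% vs 0% rows are an extreme, with every allowed loss in one arm.

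Equal removal alone does not guarantee zero bias; the shortfall must be equal too. For example, suppose 10% are removed in each arm and those removed from tDCS gain nothing from it. The true intention-to-treat difference is then 0.9 × 0.7 = 0.63 SD, while imputing each arm from its completers returns 0.70 SD, an overstatement of 0.07 SD. These are again assumed values.

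**The case against.** A reader might infer that section 4f flatly contradicts the intention-to-treat analysis. It does not. Section 7 expressly anticipates early termination and missing data and keeps such participants in their randomised arm. Nothing drops them from the analysis.

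A reader might also infer that loss will depend on treatment and favour tDCS. The documents do not support that either. Participants and treating staff are blinded, and the tasks are common to both arms. Section 8 reports broadly similar tolerability:
- A cited review found side effects on active and sham stimulation hard to tell apart.
- A crossover trial of 36 participants had no intolerability, with mean pain ratings of 2.21 on tDCS and 2.14 on sham.
- In a randomised trial of 74, pain-free ratings were more frequent on active (94%) than on sham (86%), although transient scalp redness occurred in 2 active participants (6%) and no sham participant.

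Arm-dependent loss thus remains possible but is not shown.

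A third tempting step is to take 3 of 30 active participants, assume they do 0.5 to 1 SD worse than imputed, and report 0.05 to 0.10 SD (7% to 14% of 0.7 SD) as the bias. That shifts one arm only. If sham loses 3 of 30 with the same shortfall, the bias in the difference is zero.

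Three further points are fair. That outcomes are not collected after removal is the natural reading of sections 4f and 4g, but it is not stated. The imputation model is not given and may be left to the analysis plan, so it cannot be faulted here. Removals may prove few.

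What remains is that the rule as written creates avoidable gaps in the primary outcome, and no section provides for filling them with observed data.

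**Conclusion.** The point holds as a design weakness with a cheap remedy. Section 4f undercuts the intention-to-treat aim of section 7: some randomised participants would contribute only imputed values for the primary endpoint when observed values could often be had. The gaps may be informative. Their direction and size cannot be fixed from the documents: the bias is zero with equal removal and equal shortfall in both arms, and about 0.025 to 0.10 SD (4% to 14% of the design effect) with 15% vs 5% removed and a shortfall of 0.25 to 1.0 SD. Removal rates and shortfalls are assumptions throughout, as is an imputation that does not recover the missing outcomes.

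**What to change.** Reconcile section 4f with section 7 by separating the end of study treatment from the end of study participation.
- Leave the decision to end stimulation or therapy as it is.
- Keep these participants enrolled and invite them to Visits 20 to 23 unless they withdraw consent.
- Set Visit 20 for them at one pre-specified time, for example 1 week after the planned end of treatment. Fifteen sessions at 3 to 5 per week take 3 to 5 weeks, so the last session attended and the planned end can lie weeks apart, and the choice should not be left open.
- Analyse them as randomised, and reserve multiple imputation for outcomes that could not be obtained.
- Bring section 4g into line, so that it mentions continued assessment as well as usual care.

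The cost is a short amendment and a few assessment visits for participants who would otherwise have left. These visits are already in the schedule, and section 4a allows them by telemedicine where appropriate. The planned 60 participants need not change.
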